### Usual care

Participants who are assigned to the control group will receive the standard service provision currently provided by the NGOs. Currently, the two local NGOs offer regular outreach visits and voluntary HIV/ STIs screening. Some FSWs also choose to join activities organised by the NGOs (e.g. yoga, English class or gathering). For this study, the usual service provision includes outreach visits made by the NGOs (usually the same venue will be visited once to twice a month), attending HIV/STI screening, and social activities according to their own needs and schedule. The nature of these contacts initiated by the outreach workers or sex worker themselves will be recorded. They will be advised not to join any additional psychological programmes during the study period or they have to leave the trial.

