## Methods & design

### Study design

This is a randomised controlled trial in which participants will be randomly assigned to either intervention group or usual care as the control group. Participants in the intervention condition will receive the 6-session PREP, whereas participants in the control group will receive usual care. Outcome measures of all participants will be collected at baseline, completion of intervention or 6 to 12 weeks after baseline for control group, and 3 months thereafter.

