### Participants

FSWs who fulfil the inclusion criteria will be invited and have the study explained to them by the trained outreach staff of the NGOs. Inclusion criteria for the proposed study are: (i) 18 years or older; (ii) acknowledged to have been living and working as a FSW in Hong Kong within the preceding 6 months; and (iii) able to give an informed consent. All potential participants will be screened over the telephone by one of the researchers who is a clinical psychologist to confirm their fulfilment of inclusion criteria and exclude them if they are (i) unable to speak Cantonese/ Putonghua; and (ii) diagnosed with and currently on medical or psychological treatment for a serious psychological health problems such as psychosis, current substance abuse, bipolar disorder, severe affective disorders or have suicidal ideation.

Eligible participants will be provided with further details of the study and those who provide verbal consent will complete the self-reported baseline questionnaire face-to-face. Participants will be randomly allocated on a 1:1 ratio into one of the two groups according to a block randomisation list which was computer-generated. Participants are informed that they would have an equal chance of allocating into any of the two groups and the allocation outcome is unknown to participants until baseline assessment session. The women recruited will be advised not to disclose the content and activities of the intervention to others to avoid contamination. An independent researcher will conduct the baseline, post-intervention, and follow-up assessments and enter the data obtained from the questionnaires.

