### Sample size

Sample size estimation is based on the “always” use condom rate during commercial transactions in the last month at 49.3% from the latest local study published on the topic [16] and an assumption of effect size of 25% on condom use rate between the intervention and control groups from a previous study [43]. In order to detect such a difference with a power of 80% and a two-tailed significance of 0.05, the sample size required is 66 in each group.

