### Data analyses

First of all, the baseline demographics of the intervention and control groups will be compared with independent sample *t*-tests for continuous variables and *chi*-square for categorical variables to assess the compatibility of the two-trial arms at baseline to ensure both groups were similar to start with. The change of scores on sexual health risks and psychological outcome measures (self-esteem, self-efficacy, coping, resilience and GHQ) over time between two groups will be analysed using analysis of variance with intention-to-treat analysis. Bivariate correlation analyses will be performed to examine the relationship between psychological variables and behavioural outcomes. Linear regressions will also be used to examine the associations and the effects of resilience, self-esteem, self-efficacy, coping on psychological health outcomes and HIV preventive behaviours. The statistical analyses will use SPSS 20.0 and *p*-values of 0.05 or less will be considered statistically significant.

The second objective of the current study is to explore the mechanism of how individual resilience factors influence the psychological outcomes and HIV preventive behaviours in FSWs (as proposed in Figure 1). Structural equation modelling (SEM) identifies connection strengths that best predict the observed structure of the data with respect to the specified model. Thus, SEM will be performed to evaluate the model fit of the proposed model that links psychological resources with harm-reduction behaviours as measured by condom use.

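### The rule that control participants who join another psychological programme must leave the trial creates avoidable missing outcomes and is in tension with the intention-to-treat analysis

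*Protocol article*

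**What the plan says.** The Usual care section opens with the control group as its subject: "Participants who are assigned to the control group will receive the standard service provision currently provided by the NGOs". It lists outreach visits, HIV/STI screening and social activities, says that these contacts will be recorded, and closes with the rule at issue: "They will be advised not to join any additional psychological programmes during the study period or they have to leave the trial".

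The Intervention procedure section has no equivalent sentence for women allocated to PREP.

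Under Data analyses, changes in sexual risk and psychological scores between groups "will be analysed using analysis of variance with intention-to-treat analysis". Allocation is 1:1 (Participants). Controls are assessed at baseline and then at "completion of intervention or 6 to 12 weeks after baseline for control group, and 3 months thereafter" (Study design), so the rule can act over several months.

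The Limitations section recognises that motivated women allocated to usual care may be more inclined to drop out. It gives no rate.

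**The concern.** Intention-to-treat means that each woman is analysed in the arm to which she was randomised, whatever she does afterwards. That needs her outcome, or a defensible way of handling its absence. A rule that ends her participation because of something she did after randomisation removes later outcomes that could otherwise have been collected.

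The trigger is unlikely to be unrelated to outcome. The Background and the aims argue that distress, self-esteem and coping drive condom use and self-care. A woman who seeks psychological support during follow-up may be more distressed than her peers, or better at looking after herself. Either would relate her leaving to the primary outcome.

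If the rule acts on controls only, or mainly on them because PREP women already receive psychological sessions, the loss is uneven between arms. It would add to the usual-care dropout that the Limitations section already names as a possibility. What is at stake is comparability of the arms at follow-up and, to a lesser degree, power.

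**Working it through.** **1. The plan's own figure.** Inputs from the Sample size section: always-use rate 49.3%; "an assumption of effect size of 25% on condom use rate between the intervention and control groups", read as 25 percentage points (74.3% against 49.3%); 80% power; two-sided 0.05.

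- Uncorrected: n = [1.96·√(2 × 0.618 × 0.382) + 0.842·√(0.493 × 0.507 + 0.743 × 0.257)]² / 0.25² = 58.1, so 59 per arm.
- With continuity correction: n' = (58.1/4)·[1 + √(1 + 4/(58.1 × 0.25))]² = 65.9, so 66 per arm.

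The stated 66 is reproduced. It also equals 59/0.90 rounded up, but the article states no dropout allowance, so that route is only a possibility.

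**2. Bias among those remaining (assumed inputs).** The document gives neither the share of controls who would leave (f) nor their always-use rate (p). Take 49.3% as the rate for all controls, and suppose leavers contribute no outcome at the assessment in question.

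Remaining control rate = (0.493 − f·p)/(1 − f)

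Shift in favour of PREP = f·(p − 0.493)/(1 − f)

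| f | p | Remaining control rate | Shift (points) |
|---|---|---|---|
| 10% | 65% | (0.493 − 0.065)/0.90 = 47.6% | +1.7 |
| 10% | 75% | (0.493 − 0.075)/0.90 = 46.4% | +2.9 |
| 15% | 65% | (0.493 − 0.0975)/0.85 = 46.5% | +2.8 |
| 15% | 75% | (0.493 − 0.1125)/0.85 = 44.8% | +4.5 |
| 10% | 49.3% | 49.3% | 0 |
| 10% | 30% | (0.493 − 0.030)/0.90 = 51.4% | −2.1 |

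The sign is that of p − 0.493, and the document does not inform it. At f = 10% and p = 65-75% the shift is 1.7/25 to 2.9/25, roughly a tenth of the planned 25-point difference.

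**3. Power.** Use the continuity-corrected calculation with 66 in the PREP arm and 66·(1 − f) controls. Power is 80.1% with no loss, 77.7% at 10% loss (about 59 controls) and 74.8% at 20% (about 53). The power cost at modest loss is small.

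**4. The two statements side by side.** Usual care says that a woman who joins another programme must leave. Data analyses says that the comparison is by intention-to-treat. The article does not say that a woman who leaves is still assessed, or how she is counted. Both statements can be honoured only if she stays in the analysis with outcomes that the rule itself has caused to be missing.

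**The case against.** The strongest reply is that leaving the trial is not the same as being deleted from the analysis. A woman could stop participating and still be counted in her randomised arm, with missing values handled statistically. How withdrawals are handled is usually set out in a full protocol or analysis plan that is not shown here. This stands in part: silence on missing-data methods is not a fault. The point is instead that the article states a rule which manufactures missing outcomes. Imputation can make up for them only as far as the observed data explain who left.

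Four stronger readings are tempting, and the text does not support them.

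- A reader might infer that the rule expressly exempts the PREP arm. It does not. One-arm scope rests on placement and on the absence of a counterpart.
- A reader might infer that a woman who leaves has no outcome at all. One who joins a programme after the second assessment has already given her post-intervention data and loses only the later measurement.
- A reader might infer that the comparator becomes women who sought no other help. Controls remain free to use the outreach, screening and social activities listed, and none of those is described as a psychological programme.
- A reader might infer a bias towards PREP. The sign is unknown.

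It is also fair that advising women against other programmes, and screening out those already in treatment for serious problems (Participants), may make the rule rarely triggered. Protecting the contrast between arms is a legitimate aim. Neither argument requires that follow-up end.

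**Conclusion.** The point holds in a limited form. As written, the Usual care rule requires withdrawal after randomisation for behaviour related to the constructs under study, apparently in the control arm only. It produces avoidable and possibly informative missing outcomes, and it is in tension with the intention-to-treat analysis. It does not prove that women will be excluded from the analysis, so an outright contradiction is more than the text supports.

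Size and direction cannot be determined from the document. The figure of about 2 to 3 points assumes that 10% of controls leave, that 65-75% of them would have been always-users against 49.3% overall, and that their outcomes are simply absent. It reverses if leavers have lower use and vanishes if they resemble the rest. The calculation does not show that the trial's conclusion is threatened. The case for change is that the loss is self-imposed, cannot be recovered afterwards and is cheap to prevent.

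**What to change.** Reconcile the Usual care and Data analyses sections. Keep the advice not to join other psychological programmes, but replace the clause that makes joiners leave with a statement that:

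- joining such a programme is recorded, in both arms, as a co-intervention or protocol deviation;
- women who are willing continue all scheduled assessments;
- they are analysed in the arm to which they were randomised.

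A sensitivity analysis that takes account of co-intervention may be added but is optional. The change concerns follow-up and analysis, not what support a woman should receive.

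The cost is about one sentence of protocol text and a short question at each follow-up. The question is needed because the Usual care section records contacts with the NGOs' own services, and Table 2's general reference to services received does not say that outside psychological programmes are covered. The statistical downside is some dilution of the contrast if controls who join other programmes benefit from them.

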### Measures

This study will be evaluated based on a complex intervention evaluation framework . According to the guideline on developing and evaluating complex interventions published by the Medical Research Council [44], this evaluation will involve three dimensions, including assessing the effectiveness of the programme, evaluating process and assessing cost-effectiveness. As for the effectiveness of the programme, the assessment will mainly include questionnaires eliciting socio-demographic information, psychological functioning, sexual health behaviours, and programme feedback (detailed below). The questionnaires will be self-administered, with an independent rater present to clarify or assist the completion if requested.

### Effectiveness assessment - primary outcome measures

#### HIV preventive behaviour

Self-reported rate of always using a condom during vaginal sexual intercourse with clients in the previous month and at the last encounter will be used as proxy measures of safe sex behaviour and HIV prevention.

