**Methods:**

A total of 132 FSWs will be recruited and randomly assigned to either the intervention or usual care (control) groups in a multi-centred randomised controlled trial. Based on the resilience framework, this intervention is comprised of six weekly sessions focused on the awareness, expression and management of emotions, identifying roles and personal strengths, and effective problem-solving skills. Complex intervention assessment on both intervention process and effectiveness will be adopted when the primary outcome reduction of sexual risk behaviour and other psychological outcomes include their perceived stress, self-esteem, self-efficacy, coping overall resilience, and psychological distress will be measured at baseline, post-treatment and 3-month post-intervention and differences assessed by ANOVA. The relationship of resilience factors, psychological health and HIV preventive behaviours will be evaluated using structural equation modelling.

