#### Research aims and objectives

The Personal Resilience and Enrichment Programme (PREP) has been developed according to resilience framework for a trial with FSWs in Hong Kong. The aim of this study is to seek a new direction for HIV prevention by investigating the effectiveness of PREP in FSWs. Through promoting FSW psychological health, it is hypothesised FSWs will take better care of their physical well-being and actively practise HIV preventive measures, and hence reduce their HIV risks. Specifically, the objectives of this study include:

1. To evaluate the effectiveness of PREP, the resilience-promoting intervention, in enhancing FSWs’ overall resilience, reducing their psychological distress, and eventually reducing HIV risk behaviours among FSWs in Hong Kong.

2. To explore the mechanism of how individual resilience factors operate to promote better psychological outcomes and decreasing HIV infection among FSWs.

This study is a randomised controlled trial to test the hypothesis that the participants in intervention group, as compared to those in the control group receiving usual care, would have an improvement in HIV preventive behaviour through the increase in overall resilience and in terms of their self-efficacy, self-esteem and coping strategies. At the same time, it is hypothesised that this cohort of FSWs’ psychological distress would be reduced upon completion of the programme and such improvements would be continued at least in the 3-month post-intervention period. The study will further explore the operation of the resilience model by specifying the association of stress perceived by FSWs, and the effects of the resilience attributes (self-esteem, self-efficacy, and coping strategies) on their level of psychological health and HIV preventive behaviours (Figure 1).

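### Two unranked primary condom-use measures, two follow-up times with neither named primary, and an unadjusted 0.05 threshold do not match a sample size built for one comparison

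*Protocol article*

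**What the plan says.** - **Measures.** Under the plural heading "Effectiveness assessment - primary outcome measures", the subsection on HIV preventive behaviour gives the outcome as "Self-reported rate of always using a condom during vaginal sexual intercourse with clients in the previous month and at the last encounter". That is two measures, and the section does not order them or say whether one or both must succeed.
- **Times.** Study design collects outcomes at baseline and then at "completion of intervention or 6 to 12 weeks after baseline for control group, and 3 months thereafter". The Abstract (Methods) says that outcomes "will be measured at baseline, post-treatment and 3-month post-intervention and differences assessed by ANOVA". Neither follow-up is singled out.
- **Analysis.** Data analyses compares change over time between the groups by analysis of variance, by intention to treat. It treats p-values "of 0.05 or less will be considered statistically significant". It states no adjustment and no testing order.
- **Sample size.** That section uses a 49.3% rate of consistent condom use in the last month, an effect of 25%, 80% power and two-tailed 0.05, and arrives at 66 per group. Last-encounter use plays no part in it.

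**The concern.** The sample size fixes one decision: a single measure, compared once, at 5%. The outcome and analysis sections leave more than one route to a positive primary result. Past-month use or last-encounter use could carry it, and so could the completion visit or the 3-month visit. If any of these may support the statement that PREP improves condom use, the chance of a false positive is above the 5% on which the trial was planned. Once outcome data have been seen, nobody can show that the choice among these readings was made without regard to the results. The identity and timing of the primary outcome belong in the protocol. This article has a section for them and fills it with two unranked measures.

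**Working it through.** **1. Reproduce the stated sample size.** Inputs from Sample size: p1 = 0.493; p2 = 0.743 (reading 25% as percentage points); two-sided 0.05; 80% power; 1:1 allocation (from Participants).

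- Mean proportion = (0.493 + 0.743)/2 = 0.618.
- n = [1.96·√(2·0.618·0.382) + 0.8416·√(0.493·0.507 + 0.743·0.257)]² / 0.25² = (1.347 + 0.559)² / 0.0625 ≈ 58.1, so 59 per group.
- With continuity correction: (58.1/4)·[1 + √(1 + 4/(58.1·0.25))]² ≈ 65.9, so **66 per group**.

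This matches the protocol exactly, so the trial is sized for one comparison at two-sided 0.05.

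**2. Error rate if any one success counts.** For k independent tests at 0.05 the rate is 1 − 0.95^k.

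- k = 2 (one test per measure): 1 − 0.95² = 9.75%.
- k = 4 (two measures at two visits): 1 − 0.95⁴ = 18.5%.

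The measures and visits will be correlated. The protocol gives no correlations, so a range is assumed. The values below come from 1,000,000 simulated draws of normal test statistics, with the same correlation r between measures and between visits. The r = 0 entries in the two-sided columns are from the formula.

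| r | Two tests, two-sided | Four tests, two-sided | Four tests, PREP's favour only |
|---|---|---|---|
| 0 | 9.75% | 18.5% | 9.6% |
| 0.5 | 9.0% | 16.2% | 8.1% |
| 0.7 | 8.4% | 13.7% | 6.9% |
| 0.9 | 7.0% | 9.8% | 4.9% |

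The comparators for a single test are 5% two-sided and 2.5% in PREP's favour. Two tests therefore give 1.4 to 1.95 times the nominal 5%, and four tests give about 2.0 to 3.7 times. An omnibus group-by-time test over three occasions has no single direction, so no in-favour figure is given for the two-test case. For such tests the correlated values are approximations.

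**3. What an adjustment would cost.** With the step 1 formula and continuity correction, Bonferroni for two measures (0.025 each) needs 79 per group, and for four tests (0.0125 each) 91 per group. If 66 per group is kept, power without continuity correction falls from 85% to 77% and 68%. A split of alpha added later would not fit the published size.

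**4. Recall window at each visit.** Six sessions have five gaps. Intervention procedure allows one to three weeks per gap, so the programme spans 5 to 15 weeks (5 weeks on the weekly schedule in the Abstract). A month is about 4.3 weeks, so at completion the past-month window lies inside the programme under any of these schedules. Three months later it lies wholly after it.

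**The case against.** A reader might infer that each measure is tested at each visit, and so that the error rate is two to three times 5%. The document does not support that as a statement of fact. It plans an ANOVA of change over time, most naturally one group-by-time test per measure, and on that reading the rate stays below twice 5%. The two-sided rates also include false findings against PREP, so they overstate the chance of wrongly declaring benefit.

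A reader might also take the aims' statement that "such improvements would be continued at least in the 3-month post-intervention period" as making both visits decisive for condom use. That sentence concerns psychological distress. Extended to condom use, it would describe a sustained effect, not success at either visit.

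Other points on this side have some weight:

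- The rule that any one success suffices is itself an inference. A requirement that both measures succeed would remove the inflation across measures. No such requirement is stated.
- The sample size points to past-month use as the lead measure, and the Abstract speaks of the primary outcome in the singular. The outcome section does not follow through on either.
- A multiplicity rule may stand in a full protocol or analysis plan that is not shown. That answers a complaint about missing detail. It does not remove the mismatch between the stated outcomes and the stated sample size.
- The recall-window argument is weaker with longer spacing. At three-week gaps the first four of the six sessions precede the final month. The argument also does not bear on last-encounter use.

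**Conclusion.** The point holds in limited form. The primary outcome is not reduced to one comparison, the significance threshold is unadjusted, and the sample size allows for one comparison only. If either measure may carry the claim, the two-sided false-positive rate is about 7-10% under the planned ANOVA read as one test per measure. It is about 10-18.5% only if each visit is tested separately. In PREP's favour alone, four separate tests give about 5-10%, against 2.5% for one. All of this rests on assumed correlations of 0 to 0.9 and on the any-one-success reading, which the text permits but does not state.

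**What to change.** In the primary outcome section, name consistent condom use with clients over the past month as the single primary outcome at one stated time. The 3-month follow-up is suggested for the recall-window reason above; completion could be chosen instead, provided that it is named before outcome data are seen. In Data analyses, state that this one between-group comparison is tested at two-sided 0.05. State also that last-encounter use and the other visit are secondary, tested in a fixed order or reported with confidence intervals.

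The cost is about two sentences. No extra participants are needed, because the chosen measure is the one that already sizes the trial. The downside is that an effect seen only post-treatment, or only at the last encounter, can no longer be claimed as the primary result.
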